### Outcomes

#### Visual Analog Scale (VAS) itch score

The primary endpoint will be calculated from VAS scores obtained at study visits 1 and 2 (at start and stop of therapy), asking patients to report the maximum itch intensity of the past 24 h. We are using VAS itch scores as it is the most widely used method to assess itch intensity [33]. The scale consists of a 10-cm horizontal line divided into ten equal parts numbered 0 to 10. The 0 on the left is accompanied by a smiling face and the text “no itch at all,” the 10 on the right is accompanied by a sad-looking face and the text “worst itch possible.” Mostly to promote treatment fidelity, during the 21-day treatment period, patients will be asked to keep a diary to score their itch intensity (VAS) twice daily (after waking up in the morning and before going to bed in the evening) and make notes such as the use of co-medication, side effects and other information.

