### Sample size calculation

We will compare the proportion of patients from both treatment arms who show a clinically relevant response to treatment which is defined as a reduction in itch intensity of at least 50%. Based on former placebo-controlled trials for cholestatic itch, selecting data only from patients with itch scores of 5 or higher at baseline who were treated for at least 2 weeks, we estimated that 18% of placebo-treated patients will show the defined response [30, 35, 49–51]. Based on empiric observations we believe that at least 50% of bezafibrate-treated patients will respond. Thus, we anticipate a difference in proportions between the bezafibrate and placebo groups of 32%.

Using Fisher’s exact test with alpha set at 0.05 we need 38 patients per group for a power of 0.80 for two-sided testing. Taking into account a 10% possible dropout we will include 84 patients (42 per arm) in this study. This power calculation was made after consulting a statistician and using the statistical program nQuery Advisor version 3.0.

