### Randomization and blinding

After informed consent, patients will be allocated randomly to either bezafibrate or placebo treatment (ratio 1:1) as per a computer-generated randomization schedule with randomly varying block sizes (maximum block size of 4) by the sites’ investigator through a web-based module written in ALEA (https://nl.tenalea.net, copyright NKI AVL, Amsterdam) by the AMC Clinical Research Unit. Stratification takes place for the VAS itch score at day 0 (2 strata: 5 cm ≤ VAS < 7.5 cm versus 7.5 cm ≤ VAS ≤ 10 cm). An automated email with the resulting randomization number will be sent to the trial pharmacy which allocates the patient to one of the two treatment arms and distributes the study medication accordingly to the patients, using identical packaging for placebo and bezafibrate tablets. This way, patients, physicians and outcome assessors stay blinded for treatment allocation. All investigators are aware that the pharmacy keeps the randomization list locked until all patients have completed the study, and that a request for unblinding can only be done in case a serious adverse event (SAE) occurs. Investigators at all sites keep their own subject identification log, in a secure place, and handle all personal data according to the local regulations on personal data protection.

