#### Secondary outcomes

In exploratory analyses, we will test:The absolute effect of a 3-week treatment as well as a 2-week follow-up on VAS and 5D Pruritus Scale scores (day 0 versus day 21 and day 21 versus day 35) as well as the difference of these effects between both groups (unpaired *t* tests)The effect of a 3-week treatment on daily morning and evening VAS scores in both groups separately (repeated measures analysis of variance (ANOVA) days 1–21)The difference in time at which patients reach the primary endpoint (50% reduction in itch intensity) for the first time between both groups (unpaired *t* test)The difference in morning and evening VAS scores within patients at day 1 (irrespective of treatment group, paired *t* test)The difference in the effect of a 3-week treatment as well as a 2-week follow-up on LDSI2.0 questionnaire total and subdomain scores between both groups (day 0 versus day 21 and day 21 versus day 35, unpaired *t* test)The difference in the effect of a 3-week treatment as well as a 2-week follow-up on serum ATX activity, AST, ALT, ALP, γGT, bilirubin, albumin, creatinine, CK, LDH, glucose, total cholesterol, HDL- and LDL-cholesterol and triglycerides between both groups (day 0 versus day 21 and day 21 versus day 35). Depending on the distribution of the data, parametric or nonparametric tests will be chosen, i.e., unpaired *t* test and Mann-Whitney *U* test, respectivelyThe number of AEs and SAEs during and after treatment will be listed in a table. As few AEs are expected, no statistical analysis will be applicable to compare between groups

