Although we are capturing itch intensity data using various measures in parallel (VAS, 5D and LDSI2.0 itch scores during the three visits as well as daily morning and evening VAS scores from the diaries), we endeavor to avoid the statistical multiplicity problem by having defined a single confirmatory primary endpoint, based on VAS scores during the study visits. All other data will be used in exploratory analyses only, as defined in the protocol. For example, previous studies described diurnal variation of itch intensity [2, 52] where most patients reported more intense itch in the late evening and early nighttime. By using diaries, we will also acquire information on how fast a possible effect occurs. In addition, we hope that the use of a diary stimulates compliance and increases accuracy of co-medication usage and reports of side effects.

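### Time to first 50% itch reduction is compared by an unpaired t test, with no rule for patients who have not reached it by day 21

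*Protocol article*

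**What the plan says.** Under Secondary outcomes, the protocol article lists a between-arm comparison of the time at which patients meet the primary criterion: "50% reduction in itch intensity) for the first time between both groups (unpaired *t* test". A non-parametric alternative is offered in that list only for the serum parameters.

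The times have to come from the diary, because the clinic visits fall on days 0, 21 and 35 only. The section on the VAS itch score says that "during the 21-day treatment period, patients will be asked to keep a diary to score their itch intensity (VAS) twice daily", and the Discussion states the purpose: "By using diaries, we will also acquire information on how fast a possible effect occurs".

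The Sample size calculation expects many patients not to respond by the day-21 visit: "we estimated that 18% of placebo-treated patients will show the defined response" and "we believe that at least 50% of bezafibrate-treated patients will respond".

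The Statistical analysis plan section commits to intention to treat and mentions imputation or special models for missing data in general terms. It has no rule for a patient who is fully observed and never reaches the criterion. The Secondary outcomes and Discussion sections both label this analysis exploratory.

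**The concern.** A t test needs a number for every patient it includes. A patient with a complete diary and no 50% reduction by day 21 has only a lower limit for that number: the time is censored, not missing. Read literally, the test can then use only patients who reached the criterion. Who those patients are depends on treatment, so the two subsets are no longer the randomised groups.

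Two things are at stake. The comparison may have almost no power to show an effect on speed of response. And if the drug turns non-responders into late responders, it adds long times to its own arm, so a benefit can be tabulated with a P value as slower onset.

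**Working it through.** **Inputs.** From the Sample size calculation: 18% (placebo) and 50% (bezafibrate) responding at day 21; "alpha set at 0.05 we need 38 patients per group for a power of 0.80 for two-sided testing"; enrolment raised to 42 per arm, 84 in all, as an allowance of 10% for dropout. From Randomization and blinding: "bezafibrate or placebo treatment (ratio 1:1". The observation window is the 21-day diary. The documents give no distribution of response times, so every timing shape below is an assumption.

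**The plan's own figure.** Exact power of the two-sided Fisher test at 18% v 50% is 0.785 with 37 per group and 0.800 with 38, so 38 is reproduced. 38 × 1.1 = 41.8, rounded up to 42 per arm, gives 84. No figure is stated for the time analysis.

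**How many patients have a time.**
- At the day-21 rates: 42 × 0.18 = 7.6 and 42 × 0.50 = 21.0, together 28.6 of 84 (34%). The test would lose 66% overall: 82% of placebo and 50% of bezafibrate patients.
- If more patients reach the criterion at least once on the diary (assumed 45% v 70%): 42 × 0.45 = 18.9 and 42 × 0.70 = 29.4, together 48.3 of 84, with about 43% excluded.

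**Constant hazards, 18% v 50%.** The hazard is −ln(1−p)/21, which is 0.00945 and 0.0330 per day. The mean time among reachers is 1/hazard − 21(1−p)/p:
- placebo: 105.8 − 95.7 = 10.15 days
- bezafibrate: 30.3 − 21.0 = 9.30 days

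The direction is right, but the difference is under one day. The hazard ratio is ln(0.50)/ln(0.82) = 3.49. With 28.6 events, Schoenfeld log-rank power is Φ(√(28.6/4) × ln 3.49 − 1.96) = Φ(1.38) ≈ 0.92.

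**Simulation, 42 per arm, at least 2,000 trials per scenario.**

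| Assumed scenario | t test, reachers only | t test, non-reachers set just past day 21 | log-rank, all 84 |
|---|---|---|---|
| Constant hazards, 18% v 50% | about 5% significantly faster | 82% | about 88% |
| Constant hazards, 45% v 70% | 8–9% significantly faster | not tabulated | 67–68% |
| Same 18% respond in both arms; bezafibrate adds 32% in days 8–21 | 17–83% significantly slower | 37–55% | 80–86% |

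In the last row the drug delays nobody. The share of trials significant in the wrong direction depends on when the 18% common to both arms respond: about 83% if confined to week 1, 72% for days 1–10, 52% for days 1–14, and 17% if spread over days 1–21.

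**What log-rank measures.** With 18% v 50% reaching and identical timing among reachers, log-rank is still significant in 88% of trials. Much of its advantage therefore reflects more patients responding, not earlier response.

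**The case against.** - **The plan never says that non-reachers are excluded.** This stands. With a time just past day 21 assigned to them, the t test uses all 84 and is significantly wrong in at most 0.1% of trials in these late-response scenarios. But no such rule is written, the general missing-data wording does not supply one, and this version is less powerful than log-rank.
- **The 18% and 50% are the wrong rates.** They describe the day-21 visit. A first crossing at any time on twice-daily scores will be at least as frequent on the same scale. A reader might infer that the test discards most of the trial; the documents do not establish that, and at the assumed 45% v 70% it discards about 43%. Selection by outcome remains.
- **The reversal is assumed.** A reader might infer that the test will show the drug as slower. The documents give no response times, and under constant hazards the expected direction is correct. Reversal is a possibility whose frequency varies widely with timing.
- **Speed of effect is not left wholly unstudied.** This stands. The plan also has repeated-measures ANOVA of daily VAS scores over days 1–21, though within each arm separately, so it does not replace this comparison.
- **Log-rank answers a broader question.** Also true, so 5% against 88% is not a pure measure of lost information on speed. Log-rank weakens too when hazards are far from proportional: it fell to 33% in the most extreme run (50% v 80% reaching, mean times 5.25 v 10.5 days).

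**Conclusion.** The point holds in a limited form. The protocol fixes a test that does not suit a censored time and gives no rule for patients without the event. On reachers only, about 29 of 84 patients would enter at the day-21 rates and about 48 at the assumed diary rates, in subsets shaped by treatment. The power to show a faster effect is about 5% under constant hazards at 18% v 50%. A significant result in the wrong direction is possible, in 17% to 83% of trials if the drug only adds late responders. These percentages rest on assumed timing.

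A reader might infer that the trial's efficacy conclusion is at risk. It is not: the single confirmatory endpoint is tested by Fisher's exact test on visit scores, and its sample size reproduces. Since this analysis is exploratory, the severity is minor to moderate.

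**What to change.** Replace the unpaired t test for this item with a time-to-event analysis of all randomised patients:

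- Kaplan-Meier (or cumulative incidence) curves by arm for time to first 50% reduction, with patients observed to day 21 without it censored at day 21.
- A log-rank test stratified by the day-0 VAS stratum used at randomisation.
- A Cox hazard ratio with 95% CI only as a summary, with a check of proportional hazards, because a late-response pattern would make a single ratio a poor description.
- Patients who stop for lack of efficacy kept as not having reached the criterion through day 21, in the main or a sensitivity analysis.

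The last item addresses the one small downside: censoring at the last diary entry may be informative, since the Statistical analysis plan section itself anticipates dropout for lack of efficacy. Otherwise the cost is a sentence or two. The diary data are the same, the SPSS procedures are standard, and the primary analysis and sample size do not change.

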### Fibrates in cholestatic liver diseases

Ursodeoxycholic acid (UDCA) is the only FDA- and EMA-approved therapy for PBC, improving transplantation-free survival. UDCA-responsive patients generally have similar life expectancy as sex- and age-matched controls [4]. Still, about 40% of patients do not respond to UDCA. Complementary treatment strategies are thus needed. In recent years, several case reports and pilot studies describe improvement of serum liver function tests upon fibrate treatment in patients with a suboptimal response to UDCA [5–20]. Whether or not fibrates improve transplantation-free survival in addition to UDCA remains to be proven in a currently ongoing phase III trial in PBC patients (www.clinicaltrials.gov: NCT01654731). Importantly, UDCA does not show benefit for pruritus in PBC and PSC. According to clinical observations [21], in line with some of the abovementioned reports [14, 17, 22, 23], bezafibrate does potentially have antipruritic properties. Anecdotally, itch complaints occur or recur after stopping the fibrates [21, 22].

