### Objectives

The primary objective is to determine the efficacy of bezafibrate in the treatment of moderate to severe cholestatic pruritus. Secondary objectives include efficacy in improvement of fatigue and liver disease-related quality of life and reduction of serum parameters of cholestasis, cholesterol, triglycerides and autotaxin activity. Safety will be evaluated through recording of (serious) adverse events ((S)AEs) and (suspected unexpected) adverse reactions ((SU)SARs) as well as serum parameters for kidney function and rhabdomyolysis. Also, the effect of stopping treatment on all the abovementioned variables will be assessed.

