### Criteria for withdrawal of study subjects

Increase in serum transaminases (alanine aminotransferase (AST), alanine aminotransferase (ALT)) above six times the upper limit of normal *or* an increase of three or more times compared to the start of treatmentIf serum creatinine is within the normal range at the start of the study, an increase above 133 μmol/L is considered a reason for withdrawal. In case serum creatinine is increased already at start of the study we will allow an increase of 50% of serum creatinine concentration

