#### Biological specimens

Serum will be collected from each participant at three time points: day 0, day 21 and day 35. Measurements of serum cholestasis parameters, including bilirubin, alkaline phosphatase (AP), gamma glutamyltransferase (γGT), ALT, AST, as well as albumin, lactate dehydrogenase (LDH), creatinine kinase (CK), low- and high-density lipoprotein (LDL, HDL) and total cholesterol, will be measured at the sites’ diagnostic laboratories. Furthermore, sample aliquots will be collected and stored at −80 °C until the last patient has completed the trial. Samples will be shipped on dry ice to the principal investigator’s laboratory.

Autotaxin (ATX) activity will be measured using an enzymatic endpoint assay, in which the amount of choline produced after 60 min of incubation of the sample with 1 μM of the substrate of ATX, lysophosphatidylcholine (LPC), is detected by fluorescence. Bile acid species will be determined using high-performance liquid chromatography (HPLC).

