## Discussion

The treatment of cholestatic pruritus is one of the major challenges in the daily practice of hepatologists. This, together with the promising effect of empirical bezafibrate treatment, was reason for the NASL Cholestatic Liver Diseases Study Group in collaboration with the University of Barcelona to initiate this placebo-controlled trial.

Although rifampicin is available [4], there is considerable resistance among clinicians (and patients) to prescribe (or take) rifampicin due to the risk of hepatotoxicity [26–32]. Bezafibrate would be an attractive alternative given its favorable side-effect profile and disease-modifying properties (in PBC). We choose to first show the efficacy of bezafibrate in a placebo-controlled trial before we consider continuing by showing noninferiority to rifampicin which would require many more participants. A 3-week treatment period seemed appropriate to us, as empirical observations found that this was long enough to perceive an antipruritic effect while we consider that this period of time is still ethically acceptable for patients receiving placebo, as most participants have likely suffered from itch for months or years before participation to the trial (due to, in our experience, patients’ and/or doctors’ delay and prior trial and error of antipruritic therapies). Because of this relatively short treatment duration, participants are requested not to use any rescue medication during the course of the study other than use of topical agents (e.g., menthol cream) and bile sequestrants (e.g., colestyramin), of the use of which should be noted in the diary.

It should be noted that the manufacturer of bezafibrate states that it is contraindicated in patients with liver disease. We believe, however, that with about 20 pilot studies [4–20, 22, 23] performed in patients with PBC and PSC, having increased AP levels as an inclusion criteria and all showing stable or decreasing liver transaminase levels during long-term treatment, it is safe to administer bezafibrate for 3 weeks in our target population.

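### Liver, kidney and muscle safety markers are analysed as group changes, a method with little sensitivity to a few patients with large rises

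*Protocol article*

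**What the plan says.** Under Objectives, safety is evaluated through adverse events and reactions "as well as serum parameters for kidney function and rhabdomyolysis". The same section makes "reduction of serum parameters of cholestasis, cholesterol, triglycerides and autotaxin activity" an efficacy aim.

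Under Secondary outcomes, one list serves both purposes. It names autotaxin, AST, ALT, ALP and γGT, then "bilirubin, albumin, creatinine, CK, LDH, glucose, total cholesterol" and the other lipids. Each marker is compared between arms as the change from day 0 to 21 and from day 21 to 35. On the test, the article says: "Depending on the distribution of the data, parametric or nonparametric tests will be chosen", naming the unpaired t test and the Mann-Whitney U test. The general part of the Statistical analysis plan section says that results are shown as percentage change per group with P values. Adverse events and serious adverse events are tabulated without a test.

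Criteria for withdrawal of study subjects defines harm patient by patient. For AST/ALT the limit is a value above six times the ULN, or a rise of three or more times from the start. For creatinine it is a value above 133 μmol/L if normal at the start; if already raised, "we will allow an increase of 50% of serum creatinine concentration". CK and LDH have no such limit; they appear among the measured parameters ("albumin, lactate dehydrogenase (LDH), creatinine kinase (CK" under Biological specimens) and in the list of group comparisons.

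**The concern.** Drug injury to liver, kidney or muscle usually shows as a large rise in a few patients, not as a shift of the whole arm. A t test on changes is weakened because the outliers inflate the variance. A rank test records only that those patients rank highest, not by how much. Neither summary uses the per-patient limits that the article itself sets.

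The liver tests carry a further difficulty. The article expects them to move in the favourable direction: the Background cites "improvement of serum liver function tests upon fibrate treatment", and the Discussion describes earlier studies as "all showing stable or decreasing liver transaminase levels during long-term treatment". If most treated patients fall, one figure nets benefit against injury.

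The stake is the safety statement. The Discussion notes that the manufacturer regards the drug as contraindicated in liver disease, and the abstract foresees first-line use partly because of a favourable safety profile. A non-significant group comparison of CK, creatinine or ALT should not be taken as support for that.

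**Working it through.** **The plan's own figures.** The article gives no figure for the laboratory comparisons. Its only size is for the primary endpoint, and it reproduces: two-sided Fisher's exact test, 50% versus 18%, 38 per arm, has exact power 0.8004; 38 × 1.10 = 41.8, so 42 per arm. The checks below use 42 per arm unless stated.

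**Step 1: break-even for the mean.** Suppose k of n treated patients reach 3 times baseline (a change of +2 baselines) and the others fall by a fraction f, with equal baselines. The mean change is zero when 2k = f(n − k), so f = 2k/(n − k). With n = 42:
- k = 1: 2/41 = 4.9%
- k = 2: 4/40 = 10.0%
- k = 3: 6/39 = 15.4%
- k = 4: 8/38 = 21.1%

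With 3 patients tripling, a fall of about 15% in the other 39 removes the whole signal from the mean.

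**Step 2: what the tests report for a liver test.** Assumptions, none given in the article: log-normal baseline with log SD 0.5; placebo stable; 3 of 42 bezafibrate patients at 3.2 times baseline; the other 39 fall by the fraction shown; within-patient log SD as shown; absolute change compared; 4,000 trials per setting. "Stable or decreasing" in the article covers every row, including no fall.

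| Fall in the other 39 | Log SD | Harm, t test | Harm, Mann-Whitney | Benefit, Mann-Whitney |
|---|---|---|---|---|
| 0% | 0.2 | 13% | 7% | 0.4% |
| 0% | 0.4 | 11% | 7% | 0.5% |
| 5% | 0.2 | 2% | 0.8% | 4% |
| 10% | 0.2 | under 0.1% | under 0.1% | 30% |
| 15% | 0.2 | 0% | 0% | 72% |
| 15% | 0.3 | under 0.1% | 0% | 31% |
| 15% | 0.4 | 0.2% | 0.1% | 15% |

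Each entry is the share of trials with two-sided p < 0.05 in that direction; pure chance gives 2.5% per direction. Other settings agree. With 38 per arm, log SD 0.25 and 3 patients at 3.5 times baseline, harm is flagged in 14% (t test) and 8% (Mann-Whitney) with no fall, in at most 0.4% with a 10% fall, and in 0% with a 20% fall. The t test seldom reports benefit (a few percent at most).

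**Step 3: CK.** No fall is expected. With 3 of 42 patients rising tenfold and the rest stable (log SD 0.3, assumed), harm is flagged in about 4 to 7% of trials by either test. With 1 or 2 such patients it is about 1 to 5%, near chance.

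**Step 4: what counts would show.** 3/42 = 7.1%, exact 95% CI 1.5% to 19.5%. For 0/42 the upper limit is 1 − 0.025^(1/42) = 8.4%. Fisher's test on counts with 42 per arm gives p = 0.24 for 3 versus 0, 0.055 for 5 versus 0 and 0.026 for 6 versus 0. Counts show the events; they do not give a powered test.

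**Step 5: visibility elsewhere in the article.** Serum is scheduled at days 0, 21 and 35. Day 21 is the first scheduled on-treatment sample and also the end of treatment, so a crossing found then need not appear as a withdrawal. Recruitment says that patients who drop out before day 21 are replaced; such a patient may have no day-21 value and so drop out of the group comparison.

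**The case against.** The strongest objection is that this is an omission from a condensed article. Counts over limits, shift tables and listings commonly sit in a full analysis plan, which is not shown and may contain them. That stands as a limit: a reader might infer that the trial will never count patients over its limits, and the article cannot show that. The article does, however, fix a method and a form of presentation for markers it calls safety measures, and that method suits the purpose badly.

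A second objection is that affected patients are not invisible. Adverse events and serious adverse events are tabulated, and a patient over an AST/ALT or creatinine limit is identified for withdrawal. This also stands in part. The article does not say that a crossing is recorded as an adverse event, and the sampling and replacement rules leave the gaps described above.

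A third is that masking by falling liver tests cannot apply to kidney or muscle. That is correct. Creatinine and CK are tested separately and no fall is expected in either; for them only low sensitivity remains. Even for transaminases the article says stable or decreasing, so masking is conditional on a fall that may not happen.

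Finally, the apparent-benefit figure depends on assumed inputs: at a 15% fall it drops from 72% to 15% as the log SD goes from 0.2 to 0.4, and with no fall it is under 1%. It should not be quoted alone.

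**Conclusion.** The point holds in a limited form. The stated between-arm analysis of AST, ALT, creatinine, CK and LDH has very little sensitivity to a few large individual rises. With 3 affected patients, a liver-test harm signal appears in about 6 to 14% of trials if the rest are stable and in about 0% if they fall by 15%. This low sensitivity is robust across the settings tried. For AST and ALT only, a fall in the other patients, if it occurs, can offset the rises and may read as benefit, in under 1% to about 73% of trials for falls of 0 to 15%. The falls, SDs and sizes of rise are assumptions, and a rise of three times is read as three times the starting value.

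A reader might go further and infer that toxicity would be hidden altogether, or that the trial is likely to report improved transaminases despite injury. The documents support neither: adverse events and withdrawals offer a second route, and the article does not say that a safety conclusion will rest on these P values. This is worth correcting, but it does not affect the primary analysis.

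**What to change.** Keep the t test and Mann-Whitney comparisons as exploratory efficacy analyses of the liver tests. For safety, add one table per arm covering all treated patients, including those withdrawn or replaced:
- the number and proportion whose worst post-baseline AST/ALT or creatinine (day 21, day 35 or unscheduled) meets the article's own withdrawal limits, with exact 95% confidence intervals, and the number withdrawn for that reason;
- for CK, the number above the site's ULN and the individual maximum values.

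State that these counts are descriptive, since about 6 versus 0 would be needed for p < 0.05, and that a non-significant group test is not evidence of safety.

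The cost is a few lines of text and one extra table from data already collected. It needs no new sampling and no new clinical rule. The downside is wide intervals, shown openly.

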**Discussion:**

Given its favorable safety profile and anticholestatic properties, bezafibrate may become the new first-line treatment option for treating cholestatic pruritus.

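### For adverse events the plan names only event counts and rules out any between-arm analysis; the reason given argues against a test, not against a per-patient risk difference with an interval

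*Protocol article*

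**What the plan says.** The Objectives section describes safety evaluation in two parts. The first is events: "Safety will be evaluated through recording of (serious) adverse events" and reactions. The second is laboratory values: "as well as serum parameters for kidney function and rhabdomyolysis".

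The Secondary outcomes section treats the two parts differently.

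- **Laboratory values** are compared between arms, for day 0 versus 21 and day 21 versus 35. The list includes ATX activity, AST and ALT, and continues with "albumin, creatinine, CK, LDH, glucose, total cholesterol, HDL- and LDL-cholesterol and triglycerides between both groups". The test is an unpaired t test or a Mann-Whitney U test: "Depending on the distribution of the data, parametric or nonparametric tests will be chosen".
- **AEs and SAEs** during and after treatment are to be counted and put in a table. The section then closes the matter: "As few AEs are expected, no statistical analysis will be applicable to compare between groups".

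The Sample size calculation section sets 42 patients per arm. The Recruitment section says that anyone who drops out before day 21 will be replaced. No expected AE rate appears anywhere in the article.

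**The concern.** This is a decision stated in advance, not a detail left for another document. It rests on an expectation that the article does not quantify, and nothing is provided for the case where that expectation fails.

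The reason and the rule do not match. Sparse events make a significance test uninformative. They make an interval more useful, because a short list with similar totals is easily read as reassurance when the data are compatible with a sizeable excess.

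The unit also matters. Only a number of events is named, and one patient with several events then weighs as much as several patients with one each. Replacement of dropouts adds a question about the denominator: patients who left early, possibly because of an AE, should stay in it.

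The placebo arm is the trial's only concurrent control for background symptoms. The Discussion section acknowledges that the manufacturer regards liver disease as a contraindication, and the abstract looks ahead: "Given its favorable safety profile and anticholestatic properties, bezafibrate may become the new first-line treatment option". A bound on excess AE risk from the randomised comparison would therefore be useful to readers.

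**Working it through.** **Inputs.** 42 patients per arm (Sample size calculation). Confidence level 95%, in line with the two-sided 0.05 level. The numbers of patients with an event are assumptions, because the article gives no AE rate.

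**The plan's own figure.** The only size calculation is for the primary endpoint: 18% versus 50%, Fisher's exact test, two-sided 0.05, power 0.80. Exact enumeration gives power 0.8004 at 38 per group and 0.785 at 37, so 38 reproduces. The stated 42 matches 38 × 1.10 = 41.8, rounded up. This supplies the AE denominators and nothing else; no AE power or precision is stated.

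**Step 1: no events in one arm.** The exact (Clopper-Pearson) upper limit is 1 − 0.025^(1/n). With n = 42 this is 1 − 0.025^(1/42) = 0.084, or 8.4%.

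**Step 2: difference between arms.** Newcombe's interval uses the Wilson limits (l, u) of each arm. With d = p1 − p2:

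- lower = d − √[(p1 − l1)² + (u2 − p2)²]
- upper = d + √[(u1 − p1)² + (p2 − l2)²]

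For 8/42 versus 3/42:

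- p1 = 19.05%, Wilson 9.98 to 33.30
- p2 = 7.14%, Wilson 2.46 to 19.01
- d = 11.90
- lower = 11.90 − √(9.07² + 11.87²) = 11.90 − 14.94 = −3.0
- upper = 11.90 + √(14.25² + 4.68²) = 11.90 + 15.00 = 26.9

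The same formula gives:

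| Patients with an event, bezafibrate v placebo (assumed) | Difference, points | 95% CI |
|---|---|---|
| 0 v 0 | 0.0 | −8.4 to 8.4 |
| 2 v 0 | 4.8 | −4.3 to 15.8 |
| 3 v 1 | 4.8 | −6.2 to 16.8 |
| 6 v 3 | 7.1 | −6.9 to 21.5 |
| 8 v 3 | 11.9 | −3.0 to 26.9 |

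An interval exists in every row, including the one with no events.

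**Step 3: what a test could do.** At 42 per arm, exact Fisher power of 80% needs about 23% versus 2%, 29% versus 5%, or 37% versus 10%. With no events on placebo, at least 6 are needed on bezafibrate for p < 0.05 (p = 0.026). The authors are right that testing would tell little, and this step does not touch the case for estimation.

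**The case against.** The strongest reply is that descriptive AE reporting is common and defensible in a trial with 42 patients per arm and 21 days of treatment. Whether a table shows events, patients or both is layout that a journal article may leave to the full protocol. If the table gives patients and denominators by arm, any reader can work out the difference and interval. Much of this stands and keeps the point minor. It does not remove it, because the article goes beyond silence: it names a count of events and excludes comparative analysis for a reason that does not reach estimation.

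Three stronger readings are tempting, and the documents do not support them.

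- **The safety objective ends with no between-arm comparison.** It does not. Creatinine, CK and LDH, with AST and ALT, are compared between arms, and these include the kidney and muscle parameters that the Objectives section singles out. For AEs that section commits to recording, not to an estimate of excess risk.
- **AEs will not be shown by arm.** The text excludes statistical analysis. It neither states nor bars a table split by arm.
- **The authors plan to infer safety from a lack of difference.** No section says so. The abstract refers to an existing profile, and the Discussion rests its safety argument on about 20 earlier pilot studies.

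The event counts used above are also not predictions. The 8 versus 3 case may be more than the authors mean by few, and for that reason the smaller cases are shown beside it.

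**Conclusion.** The point holds for AEs and SAEs only. The plan names a number of events and excludes any between-arm statistical analysis because few are expected. That justifies omitting a test, not omitting a per-patient difference with its interval. With 42 per arm, even zero events in an arm is compatible with a risk of up to 8.4%. Over the assumed counts in the table, the upper limit on the excess runs from 8.4 to 26.9 points. These figures rest on 42 analysed patients per arm and on assumed counts.

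Severity is minor. The primary endpoint, the sample size and the error rate are unaffected, and the laboratory part of the safety evaluation is already compared between arms. It is a cheap improvement.

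**What to change.** Replace the closing sentence of Secondary outcomes with wording such as: *For each arm, and separately for the treatment and follow-up periods, the number and percentage of randomised patients with at least one AE and with at least one SAE will be reported, with the risk difference and its 95% confidence interval (Newcombe or exact). Patients who are later replaced remain in the denominator. No hypothesis test will be made.* Keep the event list alongside it.

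The cost is one sentence and one table from data already recorded. Sample size, alpha and the single confirmatory endpoint stay as they are. The only downside is that the intervals will be wide, which is itself what a reader needs to see.
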